### EN

EN will be commenced as early as clinically feasible in both intervention groups per the CAHS Neonatology Guidelines: Enteral feeding- Initiation and progression. When EN provides 80-100% of target nutrition intake (150 mL/kg/day) or clinically appropriate, PN will be stopped by the treating clinician. EN of choice will be mother’s own milk. Standard formula milk will be used if mother’s milk supply is inadequate or if it is mother’s preference. Extensively hydrolysed formulas will be used occasionally only if clinically indicated.

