#### Secondary clinical endpoints

Duration of NICU stay (days)Duration of hospital stay (days)Duration of respiratory support [defined as mechanical ventilation via endotracheal tube OR non-invasive ventilation (NIPPV) or continuous positive airway pressure (CPAP, or humidified high-flow nasal prong (HFNP) therapy] (days)Duration of mechanical ventilation via an endotracheal tube (days)Weight, length and head circumference z scores at the time of discharge from the hospitalChanges in z scores for weight, length and head circumference from baseline todischargeTime to full EN (days). Full EN will be defined as enteral nutrition intake of ≥150 mL/kg/day.Number of hypoglycaemia episodes [blood glucose < 2.6 mmol/L] (counts)Number of hyperglycaemia episodes [blood glucose> 8.3 mmol/L] (counts)Incidence of hospital-acquired infections [defined as positive growth on blood culture or cerebrospinal fluid or sterile urine or wound swabs drawn 48 h after admission to NICU] (%)Duration of antibiotic treatment (days)Duration of ionotropic support (hours)Highest blood urea nitrogen (BUN) during hospital stay (mmol/L)Incidence of metabolic acidosis [pH < 7.25 or base excess <− 5] during hospital stay (%)Highest C-reactive protein during hospital stay (mg/L)Incidence of liver dysfunction [raised liver function tests including total bilirubin (> 200micromol/L), alkaline phosphatase (> 380 units/L), γ-glutamyltransferase (> 150 units/L), alanine transferase (> 35 units/L)] during hospital stay (%)Incidence of cholestasis [serum level of direct bilirubin> 20% of total serum bilirubin or serum level of direct bilirubin > 34 mmol/L] during hospital stay (%)

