### Statistical considerations

#### Sample size

We will recruit 60 infants (30 in each arm), which is a feasible number given that the NICU at PCH currently admits approximately 120 infants per year who would meet the eligibility criteria. Assuming the covariate-adjusted within-group standard deviation of F_2_-isoprostane levels in term/late pre-term infants is approximately 25 pg/mL [87], we would therefore have 80% power to detect a difference in early versus late PN levels of 16.2 pg/mL and 90% power to detect a difference of 19.1 pg/mL (α = 0.05). Levels of F_2_-isoprostane at birth have spanned a range of approximately 40 pg/mL across 35-40 weeks gestation [87] indicating the minimal detectable difference is clinically relevant. This study will also have adequate power to detect an increase of approximately 20% in mean phenylalanine levels in infants receiving early PN, noting that mean Day 3 levels in extremely low birth weight infants receiving aggressive nutritional therapy were at least 25% higher than that in infants receiving the standard in the study by Blanco et al. [40]. In the majority of study infants, we will collect blood through existing arterial or central venous lines. In a small number of infants (*n* = 5 to10) in whom such access is not available, we will perform venepuncture to collect the blood samples. To account for the possibility that venepuncture may be unsuccessful, we will recruit an additional three infants.

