#### Statistical analyses

Baseline characteristics of study participants will be reported as counts (percentages) for categorical outcomes, and mean (standard deviation) for normally distributed continuous outcomes or median (interquartile range) for skewed continuous outcomes.

The primary ANCOVA analyses will assess differences between the two PN groups in F_2_-isoprostane and log-transformed phenylalanine levels at Days 4 and 8. The analysis will be based on the principle of intention to treat, with the last blood plasma values carried forward for infants discharged prior to the day 8 blood collection. Covariate adjustment will be made for baseline F_2_-isoprostanes/phenylalanine, sex, gestational age, medical/surgical group, and severity of illness scores (Score for Neonatal Acute Physiology with Perinatal Extension-II (SNAPPE-II) [88].

Linear regression will be used for the analysis of the secondary efficacy outcomes (amino acid and fatty acid profiles) and growth outcomes. Trajectories of F_2_-isoprostanes, plasma amino acids and fatty acids will be examined within a mixed-effects regression framework to account for the multiple measures per infant.

Time to full EN, morbidity and respiratory outcomes (duration of hospital/NICU stay, respiratory support/mechanical ventilation) will be analysed as time-to-event data using Cox regression, with data censored at 90 days for non-survivors and survivors not reaching the endpoint within that time. Other clinical outcomes will be reported descriptively.

Appropriate regression analyses will also explore the association of the biochemical markers (F_2_-isoprostane, plasma amino acids and plasma /RBC fatty acids) with the main clinical outcomes.

Regression analyses will assess PN group differences in an unadjusted manner, as well as (jointly) controlled for risk factors including sex, gestational age, medical/surgical group, birth weight z scores and severity of illness scores (SNAPPE-II) [88]. We will investigate independent effects of 1) Medical and surgical groups; 2) Term (≥ 37 weeks’ PMA) and late preterm groups (34 to 36 6/7 weeks’ PMA). Covariate data that can be reasonably judged to be missing at random will be inferred using an appropriate method of multiple imputations.

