#### Nutrition intake

Total parenteral and enteral nutrition intakes will be recorded daily until discharge. Daily nutrition intake will be calculated based on actual intake. Full enteral nutrition will be defined as 150 mL/kg/day or exclusive breastfeeding. Energy and protein intake from EN will be calculated using CAHS Clinical Guideline (Milk Room: Breast milk fortification and preterm formula).

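### Time to full EN has two conflicting definitions, and the day-90 censoring rule, read literally, keeps discharged survivors event-free beyond the last recorded intake

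*Protocol article*

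**What the plan says.** Four places in the protocol article bear on this endpoint.

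- Secondary clinical endpoints: "Full EN will be defined as enteral nutrition intake of ≥150 mL/kg/day". No alternative criterion is given.
- Nutrition intake: "Full enteral nutrition will be defined as 150 mL/kg/day or exclusive breastfeeding". The same section fixes the observation window: "Total parenteral and enteral nutrition intakes will be recorded daily until discharge".
- Statistical analyses: time to full EN goes into a Cox model, as do length of stay and the respiratory outcomes. One censoring rule covers them all: "with data censored at 90 days for non-survivors and survivors not reaching the endpoint within that time". No other censoring time is given.
- EN: mother's own milk is the preferred feed, and "When EN provides 80-100% of target nutrition intake (150 mL/kg/day) or clinically appropriate, PN will be stopped by the treating clinician".

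The Discussion says that the trial is not powered for its clinical outcomes but expects them to indicate direction. The closing paragraph of the statistical section applies an uncorrected 0.05 threshold to all endpoints.

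**The concern.** The two definitions classify one kind of infant differently. An infant who moves to exclusive direct breastfeeding has no measured volume. That infant never reaches the endpoint under the endpoint list, but does reach it under Nutrition intake. Since mother's own milk is the first-choice feed, the group need not be negligible.

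The censoring rule makes this consequential. Day 90 suits length of stay, where discharge is itself the event. For time to full EN, discharge ends observation. Applied as written, the rule leaves a discharged survivor without a recorded event in the risk set to day 90, with no data on whether full feeding occurred. Some infants who fed well early would then count as the slowest to reach full EN. At stake is the direction of a secondary clinical result, which is what the Discussion hopes to learn from these outcomes.

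**Working it through.** **Text comparison**

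| Infant | Endpoint list | Nutrition intake |
|---|---|---|
| Recorded intake reaches 150 mL/kg/day | event | event |
| Exclusive breastfeeding, no measured volume | no event | event |
| Survivor discharged on other feeds below 150 mL/kg/day | no event | no event |

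The conflict is in the second row. The third row is possible because parenteral nutrition (PN) may stop at 80% of target, 0.80 × 150 = 120 mL/kg/day, or when judged clinically appropriate. Wherever the entry is no event, the only stated censoring time for a survivor is day 90.

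**Mechanism.** The protocol gives no event rate, hazard ratio (HR) or power for this endpoint, so there is no figure to reproduce. Let a share p of an arm be held event-free to day 90, and let S(t) be the true proportion not yet fully fed. The hazard in the analysed data is

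h(t) = (1 − p) f(t) / [p + (1 − p) S(t)], where f is the density of true times to full feeding.

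Take a true HR (late versus early) of 1.5 and p = 0.20 in both arms. With proportional hazards, S_late = S_early^1.5 and f_late / f_early = 1.5 × S_late / S_early.

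- At the start (S = 1 in both arms) the analysed HR is 1.5.
- When S_early = 0.5, S_late = 0.354. HR = 1.5 × (0.354/0.5) × (0.2 + 0.8 × 0.5)/(0.2 + 0.8 × 0.354) = 1.061 × 0.600/0.483 = 1.32.
- When S_early = 0.1, S_late = 0.0316. HR = 1.5 × 0.316 × (0.2 + 0.08)/(0.2 + 0.0253) = 0.474 × 0.280/0.2253 = 0.59.

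Both arms level off at the same 80%, so the analysed HR falls from 1.5 to below 1, and Cox regression averages over this. If the true HR is 1 and p is equal, the ratio is 1 throughout and there is no bias.

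**Size, by simulation.** These assumptions are not in the protocol: Weibull times with shape 2; early-arm median 9 days; discharge a mean of 3 days after full feeding; 0% to 30% of infants fully fed but without a measured 150 mL/kg/day. There were 20,000 infants per arm, analysed by Cox regression with Efron ties. The codings were (i) breastfeeding counts as the event; (ii) 150 mL/kg/day only, others event-free to day 90; (iii) 150 mL/kg/day only, others censored at discharge.

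| True HR | Affected, early / late | (i) | (ii) | (iii) |
|---|---|---|---|---|
| 1.5 | 0% / 0% | 1.47 | 1.47 | 1.47 |
| 1.5 | 10% / 10% | 1.50 | 1.26 | 1.43 |
| 1.5 | 20% / 20% | 1.49 | 1.20 | 1.39 |
| 1.5 | 30% / 30% | 1.48 | 1.10 | 1.31 |
| 1.5 | 10% / 20% | 1.51 | 0.92 | 1.16 |
| 1.5 | 30% / 10% | 1.49 | 1.99 | 2.00 |
| 1.0 | equal, 10% to 30% | 1.00 | 1.00 to 1.02 | 1.00 to 1.02 |
| 1.0 | 10% / 20% | 1.00 | 0.77 | 0.84 |
| 1.0 | 30% / 10% | 1.02 | 1.69 | 1.46 |

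The first row shows simulation error of about 0.03. With 30 infants per arm, 10%, 20% and 30% are 3, 6 and 9 infants. In the 10% / 20% row, a difference of 3 infants between arms moves a true 1.5 below 1.

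**The case against.** Four points can be made in the plan's defence.

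First, Nutrition intake reads like the operational definition, and the endpoint list may simply be its short form. If so, breastfed infants have the event, and only survivors leaving on other feeds below 150 mL/kg/day are carried forward. This stands as a limit on the size of the problem. It does not remove the conflict, because the article does not say which wording governs.

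Second, the day-90 sentence covers several outcomes and may be meant as an administrative cap, with early leavers handled in an analysis plan that is not shown. That is possible. But the article is not silent: it names survivors without the event and gives them one censoring time.

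Third, the affected shares have no source. This stands in full. A reader might infer that the HR will be distorted in a known direction, or that false positives will follow. The documents do not support either inference: they do not say how many infants leave without a measured 150 mL/kg/day, or that the arms differ in this. With equal shares and no true effect there is no bias.

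Fourth, this is one of many secondary outcomes that the trial says it is not powered for. That also stands, and it limits the importance of the point.

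Two further inferences should be resisted. Holding deaths to day 90 is a recognised way to treat death as an event that prevents full EN, and is not a fault. Nor does censoring at discharge alone cure the problem: discharge depends on feeding readiness, so that censoring is informative. At 20% / 20% it gives 1.39 for a true 1.5, and at 30% / 10% it gives 2.00, no better than the 1.99 under the day-90 rule.

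**Conclusion.** The point holds in limited form. The two definitions conflict in print, and the only stated censoring time for survivors lies beyond the period in which intake is recorded. Under the endpoint-list wording, applied literally, the HR for time to full EN is attenuated when a true effect exists and can be biased either way when the affected share differs by arm.

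The size and direction for this trial are unknown. The range of 1.26 to 1.10 for a true 1.5 is an illustration that rests on the assumed 10% to 30% equal shares, the Weibull shape, the 9-day median and the 3-day lag to discharge. If the Nutrition intake definition governs, most of the problem disappears. The matter is worth correcting because it is cheap to correct and because direction is what the trial hopes to learn from this outcome. The primary analyses of phenylalanine and F2-isoprostanes are not touched.

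**What to change.** 1. Use one analysis definition in both sections: 150 mL/kg/day or exclusive breastfeeding, whichever is recorded first. This is the main correction; in the illustration it recovers the true HR to within simulation error.
2. For survivors who still leave without the event, censor at the last day of recorded intake rather than at day 90, and state that this censoring is informative.
3. Add a sensitivity analysis for those infants, for example counting discharge off PN as the event, and report their number by arm.
4. Keep the day-90 convention for in-hospital deaths, and say that it is meant for them.

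The cost is wording in the protocol and analysis plan, plus recoding of intake that is already recorded daily, provided that the start of exclusive breastfeeding is captured. The price of item 2 is less nominal follow-up and a censoring assumption that needs the sensitivity analysis beside it. The choice should be fixed before outcomes are compared by arm, because it can change the result.

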### Cost analysis

The results of this RCT will be used to perform a cost-consequence analysis from a tertiary Australian public hospital perspective that utilises clinical costing under an Activity Based Funding model. We will estimate and compare direct medical costs and key clinical outcomes associated with early versus late PN. We will obtain clinical costing estimates for each participant in the trial from the CAHS Business Intelligence Unit (CAHS BIU). Like other Health Care Service Providers in WA, CAHS patient-level cost estimates are calculated by leveraging the Power Performance Manager® (PPM). Data files such as general ledger, patient encounter, transfer, diagnosis, procedure, allied health, pathology, radiology, theatre and medical are loaded into the PPM. Costs are allocated to each patient by linking services to an encounter such that volumes of usage are multiplied by corresponding unit prices of each cost category. Categories for direct medical cost include 1) hotel; 2) radiology; 3) medical/surgical supplies; 4) pathology; 5) pharmacy; 6) prostheses; 7) clinical staff (medical, nursing, allied health). As pharmacy costs, including PN cost, are not routinely calculated at a patient level, we will calculate PN and drug cost using micro-costing approach. All other cost categories are allocated at a patient level. Mean costs and 95% CI of differences in per-patient costs between the two groups will be compared for total direct medical costs and selected cost categories. Given the highly skewed distribution, which is typical of cost data, non-parametric cost comparisons will also be made.

### Data collection following recruitment

#### Blood sample collections, processing and storage

The whole blood volume of 1.4 mL will be drawn from the study infants via IV access placed for clinical purpose or by venepuncture in accordance with the CAHS Neonatology Guideline (Blood sampling: venepuncture, peripheral arterial, UAC, UVC and CVC).

After a blood sample is drawn by nursing or medical staff in NICU, the sample will be transferred on ice at 4 °C for centrifugation at 4 °C within 2 h of collection. Plasma will be extracted and transferred to small cryovials (0.2 mL for amino acid analysis, 0.25 mL for F2-isoprostanes, 0.05 mL for fatty acids). Any remaining plasma will be stored in a 4th cryovial. Following extraction of plasma from the whole blood sample, the remaining RBC cell sample will be stored in a 5th cryovial for RBC fatty acids. The samples will be stored at − 80 °C. Subsequently, the processed plasma and RBC samples will be transported to external laboratories for analyses on dry ice in an esky. We will use World Courier or Lab Taxi for deliveries to external laboratories. Each sample stored will be clearly labelled with a unique identifiable code, sample day and volume. If an infant is discharged from NICU prior to Day 8, we plan to collect the third sample on the day of discharge.

#### Plasma phenylalanine and amino acids

The concentrations of amino acids will be determined using pre-column derivatisation amino acid analysis with 6-aminoquinolyl-N-hydroxysuccinimidyl carbamate (AQC; Cohen SA, 1993, 2001) followed by separation of the derivatives and quantification by modified reversed phase ultra-performance binary liquid chromatography (UPLC; Waters Corporation; Milford, Mass. USA) employing a 12-min gradient.

Plasma, stored at − 80 °C will be thawed to room temperature and then diluted 1:1 with an internal standard (Norvaline and α amino butyric acid; Nva/AABA). The solution will be deproteinated by ultrafiltration through a membrane with a 10 kDa nominal molecular weight cut-off filter (Amicon® Ultra Centrifugal Filters, Merk Millipore). The free amino acids in the filtrate will be derivatised using the AccQ-Tag Ultra Derivatization Kit (Waters Corp) following the suppliers recommended procedures. Detection will be at 260 nm (UV). Quantitation of the amino acids will employ the Empower software (Waters Corporation) using a set of prepared standards, with Nva/AABA as the internal standard.

#### Plasma F2-isoprostanes

Plasma total F_2_-isoprostane concentrations will be measured by gas chromatography coupled to electron-capture negative-mode chemical ionisation and mass spectrometry using a modification of the previously reported method [89]. F_2_-isoprostanes in plasma (0.25 ml) will be hydrolysed under N_2_ with 1 M-KOH in methanol for 40 min at 408C. The sample will be acidified to a pH of 4.0 before being subjected to solid-phase chromatography on a pre-washed 200 mg Certify II column (Varian).

After eluting with methanol-water (50:50, v/v) and hexane- ethyl acetate (75:25, v/v), the F_2_-isoprostanes will be eluted with 2 ml ethyl acetate-methanol (90:10), dried and derivatised. F_2_-isoprostanes will be detected by selected ion monitoring using m/z 569 and m/z 573 for endogenous and tetra-deuterated internal standards, respectively.

#### Plasma and RBC fatty acids

Plasma and RBC fatty acids Plasma (0.05 mL) and BF3: Toluene: Methanol (350:300:350; 400ul) in a capped 3 ml glass vial will be vortexed and heated for 45 min at 100 °C. The samples are to be cooled and hexane (250 μl) and high-performance liquid chromatography grade water (250 μl) are added, vortex and centrifuge at 3500 rpm for 3 mins at 4 °C.The hexane fraction (30 μl) is analysed by gas-liquid chromatography. Peaks are identified by comparison with a known standard mixture. Individual fatty acids are calculated as a relative percentage with the evaluated fatty acids set at 100%.

#### Nutrition intake

Total parenteral and enteral nutrition intakes will be recorded daily until discharge. Daily nutrition intake will be calculated based on actual intake. Full enteral nutrition will be defined as 150 mL/kg/day or exclusive breastfeeding. Energy and protein intake from EN will be calculated using CAHS Clinical Guideline (Milk Room: Breast milk fortification and preterm formula).

#### Clinical data

All clinical data such as patient characteristics (e.g. main diagnosis, type of surgery received, inotrope use, antibiotics use, invasive ventilation use, non-invasive ventilation use) and secondary outcomes will be collected daily using medical records.

#### Data management

De-identified study data will be collected by the CPI and entered into a secure web-based application (REDCap®) specifically designed and built to capture, manage, and store health research data, which will be hosted on a secure server at the Telethon Kids Institute (TKI). Data collected will be accessed only by the authorised members of the study team named on the HREC application for the study. Blood samples will be stored securely at -80 °C at the TKI until the samples are transported securely to the laboratories.

### Data and safety monitoring

An independent Data and Safety Monitoring Committee (DSMC) has been established to ensure the safety of the trial participants and to monitor the quality of the study and data collection. The DSMC will comprise a Neonatologist and Senior Pharmacist who are external to PCH and are not involved in the trial. DSMC will review the study data and conduct interim analyses following recruitment of 20 and 40 participants for the key safety outcomes: incidence of hypoglycaemia, hypoglycaemia resistant to parenteral glucose administration, in-hospital mortality, neonatal mortality and any perceived life-threatening event during hospitalisation associated with the intervention.

All adverse events will be reported to the HREC of CAHS and DSMC within one business day of the first awareness of the event.

### Trial termination

The DSMC may make recommendations to stop the trial if there are concerns that either of the study interventions is harmful. We will use an unadjusted chi-square test to compare the key serious adverse events (i.e. in-hospital mortality, neonatal mortality and hypoglycaemia resistant to parenteral glucose administration) between the early and late PN groups. If there is a significant difference between the two groups, the DSMC may consider stopping the trial. Furthermore, given the known rare incidence of death during admission to NICU at PCH (i.e. 15 to 20 cases per year out of approximately 720 admissions), any death during the study will result in a pause of the study and review of death by the DSMC. The DSMC determines whether it is study-related or not before continuing the study and will stop the study if death is deemed to be related to the study.

### Ethics and dissemination

Ethics approval for all aspects of this study has been granted (RGS 0000003537). Deviation from this protocol will occur only with prior approval from HREC. The study will be conducted in accordance with the International Council on Harmonisation Good Clinical Practice guidance documents and the National Health and Medical Research Council National Statement of Ethical conduct in Human research.

The proposed interventions are minimally invasive and have negligible ethical implications for the infants assigned to the intervention groups.

As infants are unable to provide consent, informed consent will be obtained prospectively from the parent/guardian of eligible infants for the participation of their infant in the study. Great care will be taken to maintain the highest standards regarding consent for clinical research.

The CPI or a delegate will provide the parent/guardian with a trial information sheet. Trial information will be discussed in detail with the parent/guardian, and their questions will be answered in full. Once the parent/guardian are happy with the information and agree to enrolment, their signature will be taken on the Human Research Ethics Committee (HREC) approved consent form prior to randomising the infant. Optional consent will be obtained to keep any unused blood samples for future research related to the current research and to contact the parent/guardian at a later date for further research related to the current research.

Participation in this study is voluntary. A parent/guardian can withdraw their infant at any time without giving a reason. No additional information will be collected. We will use the data and samples already collected unless the parent/guardian advises us not to. The withdrawal of participation will not prejudice current or future medical treatments.

The original consent form will be filed in the study data file, the parent/guardian will be given a copy and documentation within the patient notes concerning the type of study the patient is enrolled in will occur.

The trial is registered with Australia and New Zealand Clinical Trials Registry (ACTRN12620000324910). The outcomes of this study will be submitted for publication in a peer-reviewed journal and presentation at scientific meetings. CONSORT checklist [90] will be followed for reporting the results in a journal.

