#### Blinding

Blinding of families, healthcare providers and study investigators to group allocation is not possible for this intervention. However, the laboratory personnel responsible for plasma amino acids, F_2_-isoprostanes and plasma/RBC fatty acids and the trial biostatistician will be blinded to allocations.

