#### Secondary safety endpoints

Incidence of hypoglycaemia [blood glucose < 2.6 mmol/L] (%)Incidence of hypoglycaemia resistant to parenteral glucose administration (%)In-hospital mortality [defined as death from any cause during the hospital stay] (%)Neonatal mortality [defined as death in the first 28 days from birth since birth from any cause] (%)

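### Withdrawal by a parent ends all data collection, so deaths and first episodes of resistant hypoglycaemia after that point would be missing from an open-label safety comparison

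*Protocol article*

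**What the plan says.** All references are to the protocol article.

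- **Ethics and dissemination.** "A parent/guardian can withdraw their infant at any time without giving a reason". The next sentence is "No additional information will be collected", followed by "We will use the data and samples already collected unless the parent/guardian advises us not to". No lesser step is described, and no exception is made for vital status or safety events.
- **Secondary safety endpoints.** These include "In-hospital mortality [defined as death from any cause during the hospital stay", mortality in the first 28 days of life, and "Incidence of hypoglycaemia resistant to parenteral glucose administration".
- **Data and safety monitoring; Trial termination.** The monitoring committee reviews these outcomes after 20 and 40 infants. In-hospital mortality, neonatal mortality and resistant hypoglycaemia are compared between arms by an unadjusted chi-square test. Any death during the study triggers a pause and a review.
- **Blinding.** "Blinding of families, healthcare providers and study investigators to group allocation is not possible for this intervention".
- **Clinical data.** Clinical data and secondary outcomes are taken daily from the medical records.
- **Statistical analyses.** "The analysis will be based on the principle of intention to treat", with "last blood plasma values carried forward for infants discharged prior to the day 8 blood collection". That carry-forward rule concerns early discharge, not withdrawal.

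**The concern.** The withdrawal rule is stated in absolute terms. Followed as written, it treats a parent who only wants the study blood samples to stop in the same way as a parent who wants no further use of the infant's data. An infant withdrawn early will often still be in the unit, and its glucose results, survival and length of stay continue to be charted for clinical care. The rule puts those data out of reach although collecting them needs no study procedure.

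The loss matters most for safety. The mortality windows run past a withdrawal, and a first resistant hypoglycaemia episode can also come after one. Allocation is open, and the Background section itself reports that late PN raised the risk of hypoglycaemia in the term-infant subgroup of an earlier multicentre trial. A parent whose infant has low glucose in the late arm, or deteriorates in either arm, may have a reason to leave. If that happens, missingness is related to arm and to prognosis, and the comparison seen by the monitoring committee and readers could understate harm in one arm.

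**Working it through.** The protocol article gives no figure for withdrawal, so there is none to reproduce. The check has three parts.

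**1. Does anything in the article restore follow-up after withdrawal?**

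- Ethics and dissemination: collection ends. Earlier data are kept by default, but the parent may have them excluded.
- Clinical data: records are the source, but nothing says that extraction continues after withdrawal.
- Data and safety monitoring: adverse events are reported within one business day of awareness. This captures events before withdrawal; nothing extends it to withdrawn infants.
- Trial termination: any death during the study triggers a pause. Whether a withdrawn infant's death counts is not stated.
- Sample size: the three additional infants allow for failed venepuncture, not for withdrawal.

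Nothing restores it.

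**2. What is lost and what is kept?**

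| Event | Before withdrawal | After withdrawal |
|---|---|---|
| Resistant hypoglycaemia, first episode | kept unless parent objects | lost |
| Resistant hypoglycaemia, repeat episode | – | incidence endpoint unaffected if the first episode was kept |
| Death | – | lost |
| NICU and hospital stay | – | end date not collected |

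**3. How much can one infant matter?**

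Inputs: 60 infants, 30 per arm (Sample size); 15 to 20 deaths per approximately 720 admissions (Trial termination). Applying that rate to the trial population is an assumption, because it covers all NICU admissions and the trial enrols a selected group.

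- Death rate: 15/720 = 2.1% to 20/720 = 2.8%.
- Expected deaths in 60 infants: 60 × 15/720 = 1.25 to 60 × 20/720 = 1.67.
- At the looks: 20 infants give 0.42 to 0.56; 40 infants give 0.83 to 1.11.
- One death as a share of the expected total: 1/1.67 = 60% to 1/1.25 = 80%. If only one death occurs, losing it removes all the mortality data; if two occur, half.
- One infant in an arm of 30: 1/30 = 3.3 percentage points.

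A purely hypothetical illustration with the protocol's unadjusted chi-square, X² = N(ad − bc)² / (product of the four margins), compares four events against none with three against none, as if one of the four had not been collected. For 30 per arm:

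- 4 v 0: 60 × (4 × 30)² / (30 × 30 × 4 × 56) = 4.29, p = 0.038.
- 3 v 0: 60 × (3 × 30)² / (30 × 30 × 3 × 57) = 3.16, p = 0.076.

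| Per arm | 4 v 0, chi-square p | 3 v 0, chi-square p | 4 v 0, Fisher p | 3 v 0, Fisher p |
|---|---|---|---|---|
| 10 | 0.025 | 0.060 | 0.087 | 0.211 |
| 20 | 0.035 | 0.072 | 0.106 | 0.231 |
| 30 | 0.038 | 0.076 | 0.112 | 0.237 |

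The table shows how sensitive the planned test is to one event. It does not predict event counts, and the conclusion does not depend on it.

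**The case against.** Several points on the other side stand.

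- A reader might infer that the rule contradicts intention to treat or the definition of in-hospital mortality. It does not. Intention to treat is stated alongside the primary ANCOVA analyses and means analysing infants as allocated. Missing outcomes after withdrawn consent are a limitation of follow-up, not an inconsistency.
- A reader might infer that the harm prompting a withdrawal is itself lost. Usually it is not: clinical data are collected daily, adverse events are reported within one business day, and data already held are used unless the parent objects. An infant who has already had resistant hypoglycaemia is counted. The firm loss is first episodes and deaths afterwards; the triggering event disappears only if the parent also asks for earlier data to be excluded.
- Nothing in the article says that departing from the allocated timing ends follow-up. Late PN infants who never need PN stay in their group, and intake is recorded until discharge. The rule applies to withdrawal from participation.
- The chi-square illustration is fragile. The expected count is 2 per arm when four events occur, and with Fisher's exact test none of the contrasts is below 0.05. A significant result also only allows the committee to consider stopping.
- Ending collection when consent is withdrawn is ethically accepted and was approved here. The primary endpoints are biochemical, and the Discussion says the study is not powered for clinical outcomes.

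It can also be said that graded choices may appear in the approved consent form, which is not shown. That carries less weight: the article states the rule without qualification, so this is not a detail merely left out.

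**Conclusion.** The point holds as a weakness in follow-up. As written, the article ends all collection at withdrawal and states no option to keep routine-record follow-up. Deaths and first resistant hypoglycaemia episodes after withdrawal would be missing from the safety endpoints and from the monitoring committee's comparison. This weakens the safety evidence and full intention-to-treat follow-up of clinical outcomes without contradicting either.

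That withdrawal depends on arm and on deterioration is plausible from the open allocation, but the article does not show it. With no withdrawal rate and no rate of resistant hypoglycaemia given, neither the size nor the direction of a bias can be computed. The only available scale is the expected 1.25 to 1.67 deaths, which rests on the assumption that the all-admission death rate applies. On that scale one lost death could be most or all of the mortality data. The phenylalanine and F2-isoprostane endpoints are not invalidated by this point.

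**What to change.** 1. At withdrawal, offer the parent a choice: stop the study blood samples, or leave the allocated timing, while allowing mortality, glucose and length of stay to be taken from routine records until discharge; or withdraw all data. Full withdrawal must remain available. This concerns data collection only, not the infant's care.
2. State whether the death of a withdrawn infant counts as a death during the study for the pause-and-review rule.
3. Report every withdrawal by arm and date, with the reason where the parent volunteers one, to the monitoring committee and in the final report.

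Items 1 and 2 need a protocol amendment with ethics approval, and item 1 also a consent-form amendment; item 1 needs no extra procedure or staff. Their reach is limited. By 14 November 2021, 54 infants were recruited and both interim safety reviews were complete, leaving 60 − 54 = 6 infants, or 9 with the three additional infants. Item 3 can still cover all infants and lets readers judge whether withdrawals were balanced.
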